##### Outcome measures

Our primary outcome measure is a decrease in the proportion of participants self-reporting sharing of crack pipes in the past 28 days (yes/no).

Secondary outcomes comprise:increased presentations at specialist drug services defined as: a) the change in proportion of attendances at specialist drug service sites in the past 6 months (number of new attenders in past 6 months/total number of clients) measured through data linkage to drug service records; and b) the change in proportion of participants attending a specialist drug service in the past 6 months (measured through self-report yes/no)reduction in injecting frequency defined as number of times injected in the past 28 daysreduction in number of days sharing pipes in the past 28 daysdecrease in proportion of those reporting current acute injuries defined as cuts/burns to mouth or lips in the past 28 days (yes/no)reduction in the proportion of participants who use homemade pipes in the past 28 days (yes/no)reduction in proportion of participants using ash as a crack suspension device in the past 28 days (yes/no)reduction in proportion of participants reporting respiratory risk markers defined as difficulty breathing, chest pain, coughing blood in the past 28 days (yes/no).

Our primary and most of our secondary outcomes are self-reported. Self-report measures of drug-related risk behaviours are deemed reliable, particularly when used with computer assisted survey instruments [43, 44]. The use of self-reported measures in evaluating the impact of harm reduction interventions such as NSPs is widespread [45]. Self-reported crack pipe sharing has been used as an outcome measure for Canadian studies [18, 27, 46] aiding comparability. Service presentations will be assessed through the collection of minimum identifiers (initial and date of birth) for participants in pre- and post-surveys and from each person obtaining a SIPP kit as part intervention monitoring for the process evaluation (see below). These minimum identifiers will be used to link data from surveys and SIPP monitoring, and also allow linkage of both survey and SIPP monitoring data with specialist drug services client lists before and after the intervention to review increased service presentation due to SIPP.

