In this paper, we introduce the National Institute for Health and Care Research (NIHR)-funded SIPP (Safe inhalation pipe provision) study, which commenced in July 2022 and will run until February 2025. We provide the study protocol and discuss implications for impact. To our knowledge, this study is the first of its kind globally and has been designed to meet a pressing need in the UK context, given increasing use of crack cocaine and the high prevalence of COPD among people who smoke crack and/or heroin [23, 34–36]. Alert to the heightened risk of pipe sharing and unsafe equipment use for people with respiratory vulnerabilities, members of the study team advocated for a relaxation of restrictions to allow for crack pipe provision during the COVID-19 pandemic. This application, for a government supported memorandum of understanding between police and providers, was unsuccessful due to concerns about promotion of crack use and a dearth of UK evidence [12]. The SIPP study was designed to address these concerns, with a methodologically rigorous pre- and post-intervention survey component with non-equivalent control sites, complemented by a process evaluation and peer research capacity building in geographically diverse sites, as outlined below. Our study is designed to answer the question: “To what extent and how does SIPP reduce health risks and enhance service engagement among people who use crack cocaine?”.

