**Fig. 1 Fig1:**
[figure not shown]
SIPP logic model

We employ a mixed-methods quasi-experimental design to examine whether, to what extent and how SIPP acts to reduce health risks and enhance service engagement among people who use crack cocaine. Objectives, detailed in Table 1, will be achieved through the implementation of: (1) peer-network capacity building and co-production; (2) an impact evaluation comprising a pre- and post-intervention survey with a non-equivalent control group; (3) a process evaluation comprising ethnographic observations, qualitative interviews and monitoring data; (4) an economic evaluation. Detail on each study component is provided below, after a brief outline of the SIPP intervention and study sites.

**Table 1 Tab1:** SIPP study objectives and components

SIPP objective	Study component
1. Build peer-network research capacity and explore whether the quality and impact of their SIPP engagement with PWUC differs in comparison with SIPP engagement through drug treatment services	Peer network
	Process evaluation; Impact evaluation
2. Measure the effect and cost-effectiveness of the SIPP kit on harms and risks associated with crack use (pipe sharing, presentation at drug services, using homemade pipes, cuts/burns, crack injecting)	Impact evaluation; economic evaluation
3. Evaluate SIPP fidelity, reach and acceptability in diverse specialist drug service and peer-network settings	Process evaluation
4. Explore the barriers and facilitators to SIPP uptake and service engagement among PWUC	Process evaluation
5. Explore the mechanisms through which SIPP facilitates changes in health risks and access to services, and how these are shaped by local contextual factors	Process evaluation
6. Co-develop a scalable SIPP toolkit and harm reduction resources to enhance PWUC engagement with specialist drug services and to facilitate crack-related risk reduction practices	Peer network
7. Translate evidence to policy and advocacy outputs, including to inform legislative review	All components

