##### Data collection

Two surveys will be conducted six months apart to allow for the intervention phase. For both the pre- and post-survey, a structured questionnaire will be administered by staff at specialist drug services and peer researchers, trained in data collection methods, informed consent procedures and all aspects of the study protocol. Service providers and peers will approach potential participants and current clients, describe the study and discuss contents of the information sheet and consent form. Participants who consent will complete a structured questionnaire in English on a Lenovo tablet device with the ODK collect app either self-completed or administered by a service provider or peer. The questionnaire takes approximately 30 min to complete and contains the follow sections: demographics (including age, gender identity, sexual orientation, ethnicity, and source(s) of income); drug use practices (including drugs taken, routes of administration, and equipment sharing/reuse); indicators of social exclusion (including housing status and healthcare access); policing (including recent arrest and history of incarceration); primary and secondary outcomes (see below). Our questionnaire has been developed with input from peers and service providers and incorporates measures used in comparable surveys with people who use crack in Canada and UK [2, 18, 27, 28, 30, 42] as well as drawing on a questionnaire piloted by peers in 2020 for SIPP study conceptualisation. We will not actively follow-up participants, but we will collect minimal identifiers (date of birth, initials) needed to link people over time to allow assessment of primary and secondary outcomes and new presentations at specialist drug services. The same questionnaire will be used to collect post-intervention survey data.

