##### Sample size

A sample of 306 (204 SIPP, 102 control) is sufficient to compare proportional differences in pipe sharing at 90% power with significance of *p* = 0.05. We assume 52% will share pipes, and that there will be a difference of 20% (52% to 32%) between control and intervention; substantiating previous evidence suggesting pipe provision reduces prevalence of sharing from 37 to 12% over a 6 month period [16]. An inflated sample of 740 (500 SIPP, 240 control) allows for linkage of 75% of participants between baseline and follow-up surveys and for multivariable analyses to adjust for any baseline differences in characteristics between intervention and control sites (see Fig. 3).

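### Secondary outcome (a), increased presentations, is a share of a caseload that SIPP itself can change, so it can understate a real rise in new attenders

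*Protocol article*

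**What the plan says.** Under Outcome measures, the first secondary outcome (increased presentations at specialist drug services) has two parts.

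- Measure (a) is described as "the change in proportion of attendances at specialist drug service sites in the past 6 months" and then given a formula: "number of new attenders in past 6 months/total number of clients". It comes from drug service records. Identifiers from the surveys and from kit monitoring are to be linked with "specialist drug services client lists before and after the intervention to review increased service presentation due to SIPP".
- Measure (b) is "the change in proportion of participants attending a specialist drug service in the past 6 months (measured through self-report yes/no").

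The study question in the Background is "To what extent and how does SIPP reduce health risks and enhance service engagement among people who use crack cocaine", and the Analysis section lists service engagement among the secondary outcomes to be modelled. The article does not say whether a lapsed client who comes back is a new attender. Nor does it say whether the total covers clients active in the period or everyone on the register.

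**The concern.** The label of measure (a) refers to attendances, but its formula divides one group of clients by all clients. That is the composition of the caseload. A rate of presentations would need a denominator that stays put.

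Here the denominator is taken again after the intervention, and SIPP is meant to draw people into services and keep them there. A person who stays instead of dropping out adds to the bottom only, if the total counts active clients. A new client adds to both top and bottom, so the gain is partly cancelled. A service that loses existing clients looks better.

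The control sites do not remove this. Any extra retained or returning clients that SIPP produces arise where SIPP is supplied, so the distortion enters the between-group contrast. At stake is the only record-based measure of service presentation, and therefore part of the answer to the engagement half of the study question.

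**Working it through.** **Is there a stated figure to reproduce?** Not for this outcome. The article's one sample-size figure ("A sample of 306 (204 SIPP, 102 control) is sufficient to compare proportional differences in pipe sharing at 90% power with significance of" 0.05) concerns pipe sharing. It reproduces exactly with 52% against 32%, two-sided 5%, 2:1 allocation and a continuity correction (102 control, 306 in total), and nothing below affects it.

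**Inputs.** The formula and the before-and-after lists come from Outcome measures. The article gives no caseload counts, so those used here are assumed.

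**Reading 1: total means clients active in the period, and returners are not new.** Let N be new clients and E existing clients at baseline, n the extra new clients, and r the extra returned or retained clients.

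- Measure (a) before: N/(N + E).
- Measure (a) after: (N + n)/(N + n + E + r).
- Fixed-caseload version after: (N + n)/(N + E).

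With N = 100 and E = 900:

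| n | r | Measure (a) | On fixed caseload of 1,000 |
|---|---|---|---|
| 0 | 0 | 100/1,000 = 10.0% | 10.0% |
| 50 | 0 | 150/1,050 = 14.3% | 15.0% |
| 50 | 100 | 150/1,150 = 13.0% | 15.0% |
| 20 | 200 | 120/1,220 = 9.8% | 12.0% |
| 0 | 100 | 100/1,100 = 9.1% | 10.0% |
| 0 | −100 | 100/900 = 11.1% | 10.0% |

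In the third row, 1.96 of the 5 points of true rise are lost, or 39%. The last row shows an apparent improvement from losing 100 existing clients.

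**When does the ratio actually fall?** (N + n)/(N + n + E + r) < N/(N + E) simplifies to r/E > n/N, that is r > n × E/N. With 900 existing and 100 new this is r > 9n. The threshold depends on the base. With 400 existing and 100 new (20.0%) it is r > 4n: 20 extra new and 100 returned or retained give 120/620 = 19.4%, a fall, while 20 and 50 give 120/570 = 21.1%, a rise.

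**Reading 2: active clients, but returners count as new.** From 100/1,000, 100 returners give 200/1,100 = 18.2%, a rise. Retained clients still lower the ratio and lost clients still raise it.

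**Reading 3: total means the whole register, lapsed clients included.** Assume 1,000 people already on the register plus 100 new: 100/1,100 = 9.1%. Retention does not change this, nor do returners who are not counted as new. Fifty more new clients give 150/1,150 = 13.0%, against 150/1,100 = 13.6% on the fixed register, so some dilution remains.

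**Can measure (b) carry the outcome instead?** From Recruitment, 400 + 200 = 600 of 740 participants (81%) come through the services; in the intervention sites it is 400 of 500. Assume that all service-recruited participants report attending. Then only the 100 peer-recruited participants in the intervention sites can move (b), and a 20-point rise among them shifts it by 20/500 = 4 points.

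**The case against.** The strongest reply has four parts.

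- **Undefined terms.** Neither *new attender* nor *total number of clients* is defined, and a condensed article may leave such definitions to a fuller document. This stands as far as it goes: missing definitions are not the fault here. The fault is in the stated formula, which has a denominator measured again after SIPP. Under all three readings a rise in new attenders is diluted and retention earns no credit.
- **Purpose.** Measure (a) is aimed at new people: Data collection speaks of "assessment of primary and secondary outcomes and new presentations at specialist drug services". It is fair to say that (a) need not score retention. But a measure of new presentations should then not be pulled down by retention, as it is when the total counts active clients.
- **Measure (b).** It counts any attendance in the past six months and so credits returners and retained clients. This stands, and it means that the outcome as a whole does not rest on (a). Its weight is limited by the recruitment route, though the near-ceiling level is an assumption.
- **Size.** The counts are invented, and with no returned or retained clients the loss is slight (14.3% against 15.0%).

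A reader might infer that whenever SIPP improves engagement, the outcome will read as a fall. The documents do not support that. It requires returners not to count as new, the total to mean active clients, and existing clients to grow by a larger factor than new attenders. The text fixes neither of the first two, and nothing in it suggests the third.

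**Conclusion.** The point holds as a fault in how measure (a) is built. It is a caseload share whose denominator SIPP can move, under a label that refers to attendances. If total clients means active clients, the expected distortion is dilution: 13.0% instead of 15.0% in the example. Reversal is possible only in the extreme case of r > 9n on that base, or r > 4n on the smaller one. If total clients means the whole register, the measure is blind to retention and to returners not counted as new, and the dilution is small.

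The sizes rest wholly on assumed caseloads, and the limited use of (b) on the assumption that service-recruited participants nearly all report attendance. The primary outcome and the sample size are not affected. The definition should be changed before the post-intervention lists are analysed.

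**What to change.** Keep the service records but change the quantity analysed:

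1. Take the number of new presentations in each six-month period over the site's fixed pre-intervention caseload. One suitable form is a Poisson or negative binomial model with log pre-intervention caseload as offset and a group-by-period term. In the example above the 50 extra new clients then give 150 against 100 per 1,000, however many others return or stay. Show the raw counts by site as well, since the sites are few.
2. State whether a returning client counts as new and, where the records allow, count re-presentations separately. The article mentions client lists and service records but not dated contact histories, so this part depends on what the services hold.
3. Report the number of active clients alongside, so that retention is visible, and align the label of (a) with what is counted.

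The cost is revised outcome wording and slightly more analysis work. The main count and the pre-intervention caseload are already the numerator and baseline denominator of the planned measure, so item 1 needs no new data.

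Suggested wording: *Measure (a) is the number of new presentations in each six-month period relative to the site's pre-intervention caseload, compared between intervention and control sites by period; the number of active clients is reported alongside.*

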### Study components

#### 1. Peer capacity building and co-production

Community mobilisation and capacity building are central to the SIPP project design. We adopt a multi-pronged recruitment approach, working with community-based specialist services for people who use drugs but also peer activists and networks who are experienced in delivering harm reduction interventions to their communities. Through a dynamic process of peer researcher development and community mobilisation we will capacitate and evaluate peer-led provision of the SIPP intervention alongside provision through more traditional harm reduction services. Peers (i.e. people with past and/or present experience of crack use) in three sites (Bristol, Nottingham and Birmingham) will receive training in research methods, including those specific to SIPP, and be supported by the team to deliver each study component as appropriate to their location (intervention/control). At each site, 3–5 peers will generate pre- and post-survey data with a focus on recruiting people not accessing drug treatment services, women, and ethnic minorities. During the six-month intervention period peers in the intervention sites will distribute pipes and harm reduction advice, with a focus on reaching the underserved communities recruited during survey generation. All peer researchers will be remunerated for their time and expenses, including for training participation.

People who use crack have privileged access to the communities in which they live. Our peer-network team members provide unprecedented access to people who use crack who are not in touch with services. Peers are instrumental in transferring crack risk reduction knowledge [38] and providing support in the context of drug use, homelessness and exclusion [39, 41]. This project will add value by seeking to understand the barriers and facilitators to working with peer networks as research partners to inform future community-participatory research with marginalised populations. In addition, we will explore if the mode of SIPP delivery (peer network vs. drug treatment service) influences SIPP acceptability and reduction in risk practices. This knowledge has transferable value to inform scale up of other harm reduction and public health interventions for marginalised populations (NSP, vaccine rollout, etc.).

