##### Recruitment

We will recruit up to 740 people who use crack through participating specialist drug services at the intervention (*n* = 400) and control sites (*n* = 200) and via peer networks (*n* = 140). Peer network recruitment will happen at both intervention (*n* = 100) and control sites (*n* = 40).

We will recruit using both randomised and targeted sampling. We will attempt to recruit a randomised sample from specialist drug services, to reduce selection bias, but will be pragmatic considering difficulties in recruiting this marginalised population. The LSHTM team will work with specialist drug services to generate a randomised anonymised sample of clients who are eligible to participate in the study. The specialist drug services will start recruitment from this list contacting potential clients in line with standard service engagement practice and where appropriate invite people in to participate in the research. Should we fail to meet recruitment targets at week eight, recruitment will be opened to all eligible clients, irrespective of the list, including those attending for appointments, opportunistic walk-ins and referrals from friends. In addition, we will employ targeted sampling methods to recruit 140 participants representing diverse crack user sub-populations via peer networks to widen the evidence base on health needs and service access among people who use crack not currently engaging with services. Both pre- and post-surveys recruitment will be conducted over the course of 10 weeks with an additional 4-week extension if necessary.

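### Self-reported service attendance is pooled over a sample of which 81% is recruited through those same services, so the recruitment quota largely sets its level and it should be analysed by recruitment source

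*Protocol article*

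**What the plan says.** The Outcome measures section of the protocol article gives increased presentation at services two components. Component (a) is record-based: "number of new attenders in past 6 months/total number of clients) measured through data linkage to drug service records". Component (b) is self-reported: "the change in proportion of participants attending a specialist drug service in the past 6 months (measured through self-report yes/no"). The denominator of (b) is the survey participants.

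The Recruitment section says how those participants are found: "through participating specialist drug services at the intervention (*n* = 400) and control sites (*n* = 200) and via peer networks (*n* = 140"). It splits the peer quota by arm: "Peer network recruitment will happen at both intervention (*n* = 100) and control sites (*n* = 40"). The service route starts from a list: the team and the services will "generate a randomised anonymised sample of clients who are eligible to participate in the study". If targets are not met by week eight, it opens to all eligible clients, "including those attending for appointments, opportunistic walk-ins and referrals from friends".

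The peer route has a different aim. Under Peer capacity building and co-production, peers collect both the pre- and post-intervention survey data "with a focus on recruiting people not accessing drug treatment services, women, and ethnic minorities". According to the Impact evaluation section, peer outreach runs in Bristol, Nottingham and Birmingham only.

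The Abstract gives about 740 participants at each survey point, and Data collection says participants are not actively followed up. The Analysis section uses all participants whichever survey they took part in, extends the same plan to service engagement, and lists service engagement among the a priori adjustment variables.

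**The concern.** For about four participants in five, the route into the survey is closely tied to the behaviour that 1(b) measures. Someone newly drawn into a service by SIPP and then sampled there takes a place that another client would have filled, and both would probably answer yes. A yes/no answer about the past six months also does not separate new from continuing clients. The pooled proportion can then respond weakly to a real change among people outside services, and can move when the achieved service/peer mix moves.

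Enhanced service engagement is part of the study's research question. A flat 1(b) could be read as no engagement effect, and a small rise could be read as an effect when it came from recruitment. The covariate list adds a further difficulty: adjusting 1(b) for service engagement may put the outcome, or something close to it, on both sides of its own model.

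**Working it through.** **Quota shares** (Recruitment section)

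- Total: 400 + 200 + 140 = 740. By arm: 400 + 100 = 500 and 200 + 40 = 240. These match the inflated sample in the Sample size section.
- Service-recruited share: 600/740 = 81.1% overall, 400/500 = 80.0% intervention, 200/240 = 83.3% control.
- The article gives no power or precision for 1(b). Its stated 306 (204 + 102) is for pipe sharing, 52% against 32%. It is reproduced exactly by a two-sided 5% test at 90% power, 2:1 allocation and continuity correction. It does not bear on this point.

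**Model.** Pooled proportion = w × s + (1 − w) × q, where w is the service-recruited share, s is attendance among service recruits and q is attendance among peer recruits. The article gives neither s nor q, so the values below are assumptions.

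**Dilution, intervention arm** (w = 0.80, s = 1, q from 0.40 to 0.60)

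- Before: 0.80 + 0.20 × 0.40 = 0.88
- After: 0.80 + 0.20 × 0.60 = 0.92
- A 20-point rise in peer recruits appears as 4 points. The size is 0.20 × 20 = 4 for any constant s, so it is the same at s = 0.80.

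**Mix shift, no change in behaviour** (peer share 20% to 14%)

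- Change = (0.20 − 0.14) × (s − q)
- s = 1, q = 0.40: 0.06 × 0.60 = 3.6 points
- s = 0.80, q = 0.40: 0.06 × 0.40 = 2.4 points
- s = 1, q = 0.10: 0.06 × 0.90 = 5.4 points

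**Quota difference between arms, no effect.** (0.833 − 0.800) × (s − q) = 3.3 points × (s − q): 2.0 points at s = 1, q = 0.40, and at most 3.3. A comparison of change between arms removes this if the achieved mix holds in both waves. A post-survey comparison alone does not.

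**Movement in the service route.** If s itself rose from 0.80 to 0.90, the pooled intervention figure would rise by 0.80 × 10 = 8 points. The pooled figure is therefore not immovable.

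**Power for the difference in change between arms** (two-sided 5%, no clustering, waves treated as independent, s = 1, q = 0.40 rising to 0.60 in the intervention arm only)

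| Analysis | Effect | Variance | SE | Power |
|---|---|---|---|---|
| Crude pooled | 0.04 | 0.88×0.12/500 + 0.92×0.08/500 + 2×0.90×0.10/240 = 0.001108 | 0.0333 | 22% |
| Peer recruits only | 0.20 | 2×0.24/100 + 2×0.24/40 = 0.0168 | 0.1296 | 34% |
| Stratified, each arm's own quota weights | 0.04 | 0.20²×0.0048 + (1/6)²×0.0120 = 0.000525 | 0.0229 | 41% |
| Stratified, common weight 140/740 = 0.189 | 0.0378 | 0.189²×0.0168 = 0.000601 | 0.0245 | 34% |

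Power is low in every row. The gain over the crude analysis comes from accounting for source. Discarding the service recruits adds nothing: under these inputs, stratification does at least as well as peer recruits alone. The 95% interval for the peer-stratum difference in change has a half-width of 1.96 × 0.1296 = 25 points.

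**The case against.** The strongest reply is that new engagement is already measured elsewhere. Outcome 1(a) counts new attenders from service records, and the article plans to link survey and kit-monitoring data to client lists before and after the intervention. This stands. A reader might infer that the engagement question is left unmeasured, and the article does not support that.

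A reader might also infer that only the 140 peer recruits can vary, so that 1(b) cannot show anything. This too is too strong. Listed clients may have lapsed, and walk-ins and friends' referrals need not be established clients. The attendance rate in the service route is not stated, and a change in it would move the pooled figure. The linked participants in the planned sensitivity analysis may carry some signal as well.

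Third, the quotas are the same at both surveys and change is compared with control, so the mix is constant by design, and adjustment for imbalanced variables might take in recruitment source. This stands in part. The mix shift shown above is hypothetical. But the quotas are targets, the article foresees a fallback if they are missed, and it does not commit to source as a stratum or covariate for 1(b).

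The tempting remedy, restricting 1(b) to peer recruits, does not hold. They are selected towards people not using services at both surveys, so selection on the outcome remains, in the opposite direction: peers looking for non-attenders after the intervention would tend to miss people whom SIPP had drawn in. They also come from three cities only, with Birmingham the single control city at about 40 people per wave, so the control side of that comparison rests on one city.

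**Conclusion.** The point holds as a limit on the pooled form of 1(b). The quota largely sets its level, with 80.0% of the intervention sample and 83.3% of the control sample recruited through the services in question. Change among intervention peer recruits is diluted five-fold (20 points becomes about 4). A plausible shift in recruitment mix produces a movement of similar size: 3.6 points under the stated assumptions, and 2.4 to 5.4 over the range shown.

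The shares follow from the article's own quotas. The attendance rates, the 20-point rise and the fall in peer share to 14% are assumptions. The dilution does not depend on attendance being 100% in service recruits, only on its being the same at both surveys. The documents do not support saying that 1(b) can show no new engagement, or that engagement goes unmeasured, because 1(a) is untouched. This is an inexpensive improvement to one component of a secondary outcome.

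**What to change.** 1. Analyse and report 1(b) separately for service-recruited and peer-recruited participants. Give any overall estimate as one stratified by source at fixed quota weights, the same at both surveys, and not as a crude pooled proportion.
2. Name 1(a), new attenders from service records, as the main measure of new engagement.
3. Leave service engagement out of the covariates in the model for 1(b).
4. Keep the service recruits in the analysis. Report the peer stratum with the caveat that it is selected towards non-attenders at both surveys and has one control city with about 40 people per wave.

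No new data are needed, because recruitment source is fixed by design and 1(a) is already planned. The cost is precision: intervals in the peer stratum will be wide, about ±25 points for the difference in change under the assumptions above, before clustering. The report should say so.
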